### Recruitment

Research participants will be recruited through multiple channels, including:

clinical research facilities (CRFs)clinical trial networks (CTNs)clinical research centres (CRCs)public and patient involvement (PPI) networksnational organisations, such as the Health Research Board – Trials Methodology Research Network (HRB-TMRN), Cancer Trials Ireland, and associate groups.

Colleagues within the above-mentioned networks will disseminate the survey link to potential participants. Direct contact between the researcher and survey with participants will not occur. A snowball sampling approach will be employed, whereby participants will be encouraged to share the survey link within their network [15].

In addition, the survey will be promoted via social media platforms and at public engagement events. A QR code and brief study description will be provided to enable access to the survey. To prevent duplicate responses or repeated participation, a feature in the survey software will be enabled that prevents multiple submissions.

### Informed consent

Prior to accessing the survey, participants will be provided with a participant information leaflet and consent form. Consent will be obtained by requiring participants to indicate agreement with a series of consent statements before proceeding to the survey questions (see S2 File survey participant information leaflet and consent form).

### Sample size

The survey sample has been estimated using the online Raosoft (www.raosoft.com/samplesize.html) calculator. Assuming a 5% margin of error, confidence level of 95% and response distribution of 50% were chosen, a minimum sample size of 377 respondents was estimated for large or unknown populations. Given the descriptive aims of this study and the use of non-probability sampling, the sample size is intended to provide a robust overview of public perceptions rather than population level estimates.

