#### Study participant recruitment and results write up (estimated ~ 5 months).

Estimated distribution of the survey will begin 31/05/26Estimated data collection will be completed by 30/09/26Estimated data analysis will be completed by 31/10/26.

The completed study survey will be distributed for 3 + months, or until the recruitment target (n = 377) is reached. Results from the survey will be analysed and written up for publication in a peer-reviewed open-access journal over a two-month period.

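### The stated survey inputs give 385 respondents for a large or unknown population; 377 needs a finite population of about 20,000 that the protocol never states (minor effect)

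*Protocol article*

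**What the plan says.** The Phase II Sample size section says that the number came from an online calculator: "The survey sample has been estimated using the online Raosoft" tool. The inputs follow: "Assuming a 5% margin of error, confidence level of 95% and response distribution of 50% were chosen". The result is given as "a minimum sample size of 377 respondents was estimated for large or unknown populations". No population size is stated there or anywhere else in the protocol.

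The section then limits what the number is for: "the sample size is intended to provide a robust overview of public perceptions rather than population level estimates".

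The timeline for survey recruitment uses the same number again: "The completed study survey will be distributed for 3 + months, or until the recruitment target (n = 377) is reached".

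**The concern.** The printed inputs, the description of the population and the printed result cannot all be right. For a single proportion, the required sample size rises with population size towards a ceiling. A large or unknown population sits at that ceiling, and 377 lies below it. Either the figure is wrong for the population described, or a specific finite population was entered and not reported.

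Two things follow. A reader who repeats the calculation with a large population will not obtain 377, so the sample-size statement cannot be reproduced as written. And because the timeline allows distribution to end once 377 is reached, the mislabelled number can also set when the survey closes.

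**Working it through.** **Inputs, all from the Sample size section.** Margin E = 0.05; 95% confidence, so z = 1.96; response distribution p = 0.50; population size N not given as a number.

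**Step 1. Large or unknown population (no correction).**

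n₀ = z² p(1 − p) / E² = 1.96² × 0.25 / 0.05² = 0.9604 / 0.0025 = 384.16

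The unrounded z of 1.95996 gives 384.15. Either way the answer is 385 rounded up, or 384 to nearest. It is not 377.

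**Step 2. Other ways to reach 377 without a correction.**

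- z = 2.0 gives 400.
- A one-sided z of 1.645 gives 271.
- Keeping z and E, an uncorrected 377 needs p(1 − p) = 377 × 0.0025 / 1.95996² = 0.2453, so p of about 0.43. The protocol states 0.50.

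None of these fits the stated inputs.

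**Step 3. Reproducing 377 with a finite-population correction.**

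n = N x / [(N − 1)E² + x], with x = z² p(1 − p), which is the same as n = n₀ / [1 + (n₀ − 1)/N].

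| N | n | rounded up |
|---|---|---|
| 10,000 | 369.97 | 370 |
| 20,000 | 376.93 | 377 |
| 50,000 | 381.22 | 382 |
| 100,000 | 382.68 | 383 |
| 1,000,000 | 384.00 | 384 |

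So 377 can be reproduced, but only for a modest population.

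**Step 4. Which populations give 377.** Solving the formula for N gives N = n(n₀ − 1) / (n₀ − n), with n₀ = 384.1459.

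- Rounding up (n above 376 and at most 377): 376 × 383.1459 / 8.1459 = 17,685 and 377 × 383.1459 / 7.1459 = 20,213, so N runs from 17,686 to 20,213.
- Rounding to nearest (n from 376.5 to 377.5): 376.5 × 383.1459 / 7.6459 = 18,867 and 377.5 × 383.1459 / 6.6459 = 21,763, so N runs from 18,867 to 21,763.

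Under either rounding rule, N lies between roughly 17,700 and 21,800.

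**Step 5. Size of the effect.**

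- Shortfall: 385 − 377 = 8 respondents; 8/385 = 2.1%.
- Nominal margin with 377 and no correction: 1.96 × √(0.25/377) = 0.0505, that is ±5.05%.
- Nominal margin with 385: 1.96 × √(0.25/385) = 0.0499, that is ±4.99%.

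**The case against.** The best reply is that nothing of substance depends on the difference. The protocol gives its margin as a whole percentage, and 5.05% rounds to 5%. Phase II plans descriptive statistics and content analysis, with no test, power statement or decision threshold tied to 377. The figure is called a minimum, so more responses may be collected. All of this stands, and it limits the point to a reporting correction. It does not make 377 the right number for the population described, and the timeline does allow the survey to stop there.

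Three stronger readings are tempting, but the protocol does not support them.

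- **That the survey is undersized.** Eight respondents and 0.05 percentage points of margin do not show this.
- **That readers will be misled into attaching ±5% to a network and snowball sample.** The formula does assume simple random sampling. However, the same section says that the sampling is non-probability and disclaims population-level estimates, and nothing says that ±5% will be reported with the results. No further disclaimer is needed.
- **That clustering by network makes the real margin much wider.** The protocol gives no intraclass correlation, cluster size or number of networks, so any design effect would be invented. In a sample of this kind the main worry is selection, which a design effect does not measure.

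Nor is 377 the only planning number, since Phase I aims for 8–10 PPI partners. It is, however, the only one derived from a calculation.

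**Conclusion.** The point holds as a minor error in a stated figure. For a population that is large or of unknown size, the protocol's own inputs give 385 (384 to nearest). The printed 377 is the answer for a finite population of about 20,000, which the protocol does not state and which its description contradicts.

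The conclusion rests on the standard formula for one proportion and on the three inputs as printed. The value of about 20,000 is inferred by working back from 377; the protocol does not say what was entered in the calculator.

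**What to change.** Make the same change in the Sample size section and in the survey timeline, where the text reads "or until the recruitment target (n = 377) is reached". There are two options:

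1. Restate the figure as 385 and keep the present description of the population. This suits the open eligibility (English-speaking adults with internet access) and the open distribution channels.
2. Keep 377, state the finite population that was entered (about 20,000 by back-calculation), and drop the description of the population as large or of unknown size. Without the correction, the nominal margin at 377 is ±5.05%.

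The cost is two wording edits and, under the first option, at most 8 more responses to an online survey. Distribution is planned to begin on 31/05/26 and the study is still recruiting PPI partners, so the edit can be made before launch.

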### Inclusion and exclusion criteria

Adults over the age of 18 with access to the internet will be eligible to participate. Non-eligible people include those under the age of 18, those that do not have access to the internet, or those who are non-English speakers, as the survey will be provided only in the English language.

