**Methods:**

This study is a two-phase protocol. Phase I involves the co-development of an anonymous online survey with PPI partners through two structured workshops. Survey themes, topics, questions and format will be agreed collaboratively, and the co-development process will be evaluated using qualitative data collected during the workshops. These data will be analysed thematically, using Braun & Clarke’s (2006) framework. Phase II involves distribution of the survey to clinical research, patient and public networks using an online platform. Survey data will be analysed using descriptive statistics for quantitative data and inductive content analysis for qualitative responses.

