### Survey participant population

Survey participants will comprise members of the public with links to clinical research networks, clinical research facilities, patient/charity or advocacy organisations associated to clinical research.

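### The eligibility criteria do not carry over the members-of-the-public restriction, so people who work in clinical research can respond and count toward the 377

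*Protocol article*

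**What the plan says.** Three sections of the protocol article bear on who answers the survey.

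- **Survey participant population** names the target: "Survey participants will comprise members of the public with links to clinical research networks, clinical research facilities, patient/charity or advocacy organisations". It does not define member of the public.
- **Inclusion and exclusion criteria** sets the operative rules: "Adults over the age of 18 with access to the internet will be eligible to participate". The exclusions are equally short: "Non-eligible people include those under the age of 18, those that do not have access to the internet, or those who are non-English speakers". Occupation and the public restriction do not appear.
- **Recruitment** lists clinical research facilities, trial networks, research centres, PPI networks and national organisations, among them a trials methodology network. It adds that "Colleagues within the above-mentioned networks will disseminate the survey link to potential participants" and that "participants will be encouraged to share the survey link within their network". Social media and public engagement events are further routes. The abstract summarises this as "distribution of the survey to clinical research, patient and public networks", with clinical research networks listed beside the patient and public ones.

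The first purpose given for the Phase II survey is to assess public knowledge and understanding of clinical research, including awareness of sustainable practices. The sample size section asks for at least 377 respondents. The study timeline keeps the survey open for three months or more, or until 377 is reached.

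**The concern.** The population section and the criteria section describe different groups. A trial coordinator, investigator or methodologist who receives the link meets every stated criterion, and nothing described in the article would identify that person or keep the response out of the 377.

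This matters because occupation bears directly on the first outcome. The first proposed theme in Table 1 is knowledge of what clinical research is and how it works, and people who do the work can be expected to know more about it than lay respondents. The Discussion says that limited public awareness may indicate a need for better communication and education. Mixing in informed respondents could hide that signal. The stopping condition adds to the risk: if staff answer quickly, they can use up part of the 377 before lay respondents are reached.

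The section on minimising bias does not cover this. It offers varied networks and snowballing as the remedy for sampling bias, and the only weakness it concedes is the possible loss of people outside the social connections.

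**Working it through.** **1. The plan's own figure.** Inputs from the sample size section: margin e = 0.05, confidence 95% (z = 1.96), response distribution p = 0.5.

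- Very large population: n = z²p(1−p)/e² = 3.84 × 0.25 / 0.0025 = 384.1, rounded up to 385.
- Finite population: n = N·x / ((N−1)e² + x), with x = z²p(1−p) = 0.96. With an assumed N of 20,000, which the article does not state, n = 376.9, so 377.
- Margin at 377: 1.96 × √(0.25/377) = 5.05 points.

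The figure of 377 is not in dispute here. The question is who is counted in it.

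**2. Sections side by side.**

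| Section | Restricts to the public? | Identifies research staff? |
|---|---|---|
| Survey participant population | Yes, undefined | No |
| Inclusion and exclusion criteria | No | No |
| Recruitment | No | No |
| Table 1 (proposed themes) | Not applicable | No respondent-background topic |
| Phase II data extraction (analysis) | No | No separation by role mentioned |

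**3. Size of the possible bias.** Let w be the share of respondents who work in clinical research, and let g be the difference in awareness between them and the public (p_prof − p_pub). The pooled proportion is w·p_prof + (1−w)·p_pub, so

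bias = w × g.

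Neither w nor g is in the documents. The assumed range is public awareness of 30% to 50% and professional awareness of 80% to 90%, so g runs from 30 points (80 − 50) to 60 points (90 − 30).

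| Share w | Bias at g = 30 | Bias at g = 60 |
|---|---|---|
| 10% | 3 points | 6 points |
| 20% | 6 points | 12 points |
| 30% | 9 points | 18 points |

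The share at which the bias equals 5 points is w = 5/g:

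| Gap g | Share w |
|---|---|
| 30 points | 16.7% |
| 40 points | 12.5% |
| 50 points | 10% |
| 60 points | 8.3% |

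If w or g is zero, so is the bias.

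**4. Effect on the count.** To have 377 public respondents, the total needed is 377/(1−w). If collection stops at 377 in total, 377(1−w) public respondents remain, with margin 1.96 × √(0.25/n).

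| Share w | Total needed for 377 public | Public respondents if total is 377 | Margin among them |
|---|---|---|---|
| 10% | 419 | 339 | 5.3 points |
| 20% | 472 | 302 | 5.6 points |
| 30% | 539 | 264 | 6.0 points |

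**The case against.** The best defence is that the two sections are meant to be read together: the population section names the public, and the criteria add practical conditions. On that reading, colleagues in the networks pass the link on and are not themselves the intended respondents. PPI networks, patient and advocacy organisations, social media and public events all reach lay people, which may keep the professional share low. The survey is not yet written, so a background item could still be included, and the participant leaflet, which is not shown, may say who is invited. The article also disclaims population-level estimates.

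Much of this stands as a limit on the size of the problem. It does not remove the gap. An undefined term that is absent from the criteria gives a respondent no rule to apply. The disclaimer limits generalisation from the sample; it does not justify counting research staff as public, and the same sentence still promises a robust overview of public perceptions.

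A reader might infer three stronger things that the documents do not support:

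- *That public awareness will be inflated by a known amount.* Neither the share nor the gap is given. For awareness of environmental sustainability in particular, nothing in the article shows that trial staff know much more than others.
- *That anonymity makes staff responses impossible to separate.* The anonymity commitment concerns identifiers such as IP addresses and contact details. A non-identifying role question is compatible with it. Separation fails only if no such question is asked.
- *That anyone who has ever worked in research must be excluded.* The population section deliberately seeks people with research links, and former staff may properly belong to the public group.

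**Conclusion.** The concern holds as a mismatch between the stated population and the operative criteria. People who work in clinical research are eligible, can plausibly be reached by the recruitment routes, and would count toward 377 in a survey whose first purpose is to measure public knowledge. Upward bias in knowledge of clinical research is the logical direction if they respond. It is a risk, not an established result.

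Under assumed awareness gaps of 30 to 60 points, a professional share of about 8% to 17% would shift a proportion by 5 points. That margin is only a yardstick, since the sample is not a probability sample and the article names no single headline proportion. The correction is worth making because it is nearly free before the questionnaire is final, whereas anonymous responses collected without a role item cannot be reclassified later.

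**What to change.** 1. Define member of the public in *Survey participant population* and carry the same definition into *Inclusion and exclusion criteria*, so that the two sections agree.
2. Add one non-identifying question straight after consent. Suggested wording: *Do you currently work in the conduct, management, funding or methodology of clinical research? (yes / no)*.
3. Let those who answer yes complete the survey, but report them as a separate group. Base the public-understanding results on the remaining respondents.
4. State in *Sample size* and *Study timeline* that the 377 target and the stopping condition apply to the remaining respondents.

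The cost is one extra question, a line in the criteria and possibly in the participant leaflet, and somewhat slower recruitment: about 419 responses in total if 10% are professionals, or 472 if 20% are. The study is still recruiting PPI partners, so the question can be worded and tested in the planned workshops and user testing.

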### Strategies to minimise bias

Survey based research is subject to several potential sources of bias including response bias, sampling bias, non-response bias and order effects.

*Response bias* will be mitigated through the co-development of the survey content with PPI partners ensuring the language is simple and clear, accessible and avoids leading questions. The survey distribution approach will ensure a wide pool of potential participants are reached and respondents are anonymous which will further reduce risk of response bias.

*Sampling bias* will be addressed by distributing the survey through various clinical research and public facing networks and by using a snowball sampling approach to extend reach beyond initial distribution groups, increasing the random sampling. This approach may result in reducing representativeness in the survey population as it may exclude those that are not social connections, however the inclusion of networks with diverse connection pools, as well as adopting various distribution methods (email, social media, public engagement events) can address this.

*Non-response bias* will be minimised by designing the survey to be concise, accessible and compatible with screen reading software. As this is a web survey, non-response bias is unavoidable for those who experience difficulty with technology and online accessibility, however measures will be taken to ensure access for participants is as easy as possible.

*Order effects* will be reduced by randomising survey questions where appropriate, except where question order is required for logical coherence.

### Data extraction

Survey data will be exported from Qualtrics for analysis. Quantitative data will be analysed using descriptive statistics within Qualtrics. Qualitative free text responses will be analysed using inductive content analysis [16]. Automated text analysis tools (TextIQ) will be used to support data organisation in Qualtrics to code the data. This approach is suitable for analysing text-based data where you are not making pre-determined assumptions about the dataset, as well as data that is unknown or not previously researched. As this survey will generate new data regarding an unexplored topic, it is the preferred approach to take.

This approach differs from a deductive content analysis approach, where the researcher utilises predetermined codes and/or a previous conceptual framework to analyse data. Inductive content analysis takes a multi-step approach, including familiarising with the data, conducting multiple rounds of coding data iteratively, followed by synthesising and interpreting the data [17]. To reduce bias in this process, a peer analysis approach will be taken, where a second researcher will similarly code and interpret the data to ensure validity. If there are discrepancies between the codes generated, both researchers will discuss and resolve as appropriate. If required, a third researcher will be utilised to resolve discrepancies [13,14].

### Survey reporting

The checklist for reporting of survey studies (CROSS) will be used to guide transparent and standardised reporting of the survey findings [18]. The CROSS checklist (S3 File) comprises 40 items across 19 sections and was a checklist developed through consensus of experts, via a Delphi method [19].

### Study status

This study is at the recruitment stage for PPI partners.

### Study timeline

#### PPI partner recruitment and workshop write up (estimated ~ 6 months).

Recruitment of PPI partners began 20/01/26Estimated recruitment will be completed by 31/03/26Estimated data collection will be completed by 15/05/26Estimated data analysis will be completed by 30/06/26.

Recruitment of PPI partners will take place for approximately one month. Two workshops will be held soon after over a one-month period. Following this, data analysis and write-up of data collected during the workshops will take place over two to three months. A manuscript of the development workshop exercise will be written up over a two-month period and submitted for publication in a peer-reviewed open-access journal.

#### Study participant recruitment and results write up (estimated ~ 5 months).

Estimated distribution of the survey will begin 31/05/26Estimated data collection will be completed by 30/09/26Estimated data analysis will be completed by 31/10/26.

The completed study survey will be distributed for 3 + months, or until the recruitment target (n = 377) is reached. Results from the survey will be analysed and written up for publication in a peer-reviewed open-access journal over a two-month period.

